### Sample Size Estimation and Analysis

The sample size calculation for the assessment of CMR efficacy was based on a previous study [1], which showed that the prevalence of potentially inappropriate medications in the older adult population was 28% in India. We assume that the effect size of the interdepartmental CMR is 10%, power is 80%, and significance level is 5%. The sample size calculation was estimated to be 280 participants. Given that this study will be conducted at 2 different sites, Pondicherry Institute of Medical Sciences and Jawaharlal Institute of Postgraduate Medical Education and Research, 140 participants will be recruited from each site. Universal sampling techniques will be used to enroll participants in this phase of the study. For the qualitative component of the study to assess the implementation challenges of CMR, preferably 2 FGDs will be conducted among CMR team members at each study site. Approximately 10-16 in-depth interviews will be conducted per site until the data saturation point is reached.

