#### Secondary End Points

The secondary end points were as follows:

Costs involved in the implementation of CMR in Indian health care settings (tertiary health care settings perspective).Change in the number of potentially inappropriate medications from hospital admission to discharge due to CMR.Change in the MAI score from hospital admission to discharge due to CMR.Number of medication-related hospital admissions from the day of discharge to 30 days post discharge.

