### Data Management and Statistical Analyses

#### Quantitative Component

The investigators will ensure the completeness, accuracy, and timeliness of data collection. The study sites will enter data in the REDCap software, and case record forms will be scanned in REDCap. The data will be checked for a normal distribution (Kolmogorov-Smirnov test). Student paired 1-sided *t* test will be used to analyze the differences between MAI scores at admission and discharge to determine the effectiveness of CMR, and the chi-square test or Fisher exact test will be used to assess the differences in the frequency distribution. All analyses will be conducted via the SPSS software (version 22.0 for Windows 11; Microsoft), Microsoft Excel 2019, and STATA (version 12; StataCorp LP).

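### The 280 patients are sized for a binary PIM proportion that is missing from the end point list, and the only frequency tests named ignore the pairing

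*Protocol article*

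**What the plan says.** All references are to the Protocol article.

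- **Sample Size Estimation and Analysis.** The efficacy calculation takes a baseline "prevalence of potentially inappropriate medications in the older adult population was 28% in India". It continues: "We assume that the effect size of the interdepartmental CMR is 10%, power is 80%, and significance level is 5" per cent. The result: "The sample size calculation was estimated to be 280 participants", recruited as 140 at each of two sites. The section does not say whether the 10% is absolute or relative, or whether the test is one- or two-sided.
- **Secondary End Points.** The PIM end point is "Change in the number of potentially inappropriate medications from hospital admission to discharge", which is a count. The other prescribing end point is the change in MAI score. The primary end point is qualitative.
- **Study Design (Quantitative Component) and Follow-Up Phase.** The design is pre-post in the same patients. The first section mentions a falling percentage of inappropriate medications and the second an incidence of PIMs before and after the intervention. Neither gives a denominator.
- **Data Management and Statistical Analyses (Quantitative Component).** For the score: "Student paired 1-sided *t* test will be used to analyze the differences between MAI scores at admission and discharge". For frequencies: "the chi-square test or Fisher exact test will be used to assess the differences in the frequency distribution". No paired test for a binary outcome is named.

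**The concern.** A stated power belongs to one end point and one test. Here the inputs are those of a yes/no outcome per patient, but the end points to be reported are a count and a score. Nothing in the 28%, the 10% or the 280 gives the power for either of those. If the PIM result is null, a reader has no end point to set against the 80%.

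The test raises a second difficulty. If the proportion is reported, the plan would compare admission with discharge by a test for independent groups. A patient's PIM status at the two times is likely to be positively correlated. Ignoring that overstates the standard error of the difference and wastes the main advantage of measuring the same patients twice.

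**Working it through.** **Inputs.** From the sample size section: p1 = 0.28, effect 10%, power 80%, significance level 5%, n = 280. Assumed, because the article gives no figure: 10% is absolute, so p2 = 0.18 and d = 0.10; the test is two-sided; the within-patient correlation φ is 0 to 0.5 (the maximum possible with these margins is 0.75).

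**1. Reproducing 280.** For paired proportions (McNemar, normal approximation), with ψ the total discordant probability:

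n = [1.96·√ψ + 0.8416·√(ψ − d²)]² / d²

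At φ = 0 the discordant cells are 0.28 × 0.82 = 0.2296 and 0.18 × 0.72 = 0.1296, so ψ = 0.3592.

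n = [1.96 × 0.5993 + 0.8416 × 0.5909]² / 0.01 = [1.1747 + 0.4973]² / 0.01 = **279.6, that is 280 pairs** (power 80.1%).

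The two-sample formula for 28% against 18%, pooled and two-sided, gives 277 per group. A one-sided 5% test would need only 220 pairs, so 280 points to a two-sided calculation.

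**2. Effect of positive correlation on McNemar.** ψ = 0.3592 − 2φ·√(0.28 × 0.72 × 0.18 × 0.82) = 0.3592 − 0.345φ.

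Power = Φ{[d√n − 1.96√ψ] / √(ψ − d²)}

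At φ = 0.3: ψ = 0.2557, and [1.673 − 0.991] / 0.4957 = 1.376, giving 91.6%.

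**3. The unpaired chi-square on the same data.** The test uses SE₀ = √(2 × 0.23 × 0.77 / 280) = 0.0356, whatever φ is. The true SD of the difference is √((ψ − d²)/280).

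Power = Φ{[0.10 − 1.96 × 0.0356] / SD}

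At φ = 0.3: SD = 0.0296, and 0.0303 / 0.0296 = 1.02, giving 84.7%.

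**4. True size of the unpaired test.** Under no change, the true variance is (1 − φ) times the one the test uses, so size = 2[1 − Φ(1.96/√(1 − φ))]. At φ = 0.3: 1.96/0.837 = 2.34, giving 1.9%. At φ = 0.5: 1.96/0.707 = 2.77, giving 0.6%.

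| φ | ψ | Pairs needed (McNemar) | Power, McNemar, 280 pairs | Power, unpaired chi-square, 280 pairs | True size, unpaired |
|---|---|---|---|---|---|
| 0 | 0.3592 | 280 | 80.1% | 80.4% | 5% |
| 0.3 | 0.2557 | 199 | 91.6% | 84.7% | 1.9% |
| 0.5 | 0.1867 | 145 | 97.5% | 88.6% | 0.6% |

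**5. Sensitivity to loss.** Only patients without an assessed discharge prescription matter here, and the article gives no rate. If 10% were lost (252 pairs), McNemar power would be 75.8% at φ = 0, 79.9% at 0.1 and 84.2% at 0.2. If 20% were lost (224 pairs), a correlation of about 0.21 would restore 80%.

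**6. Units of the PIM outcome, side by side.** The sample size uses a prevalence in older adults, which reads as a proportion of patients. The end point list uses a number of PIMs. The design section uses a percentage of medications, and the follow-up section an incidence. The quantity that was powered is the one not defined as an end point.

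**The case against.** The best defence is that the arithmetic is sound. The stated inputs give 280 exactly for paired data at independence, and that is the cautious case for any non-negative correlation. This stands in full. A reader might infer that the 80% holds only if the two assessments are uncorrelated and nobody is lost, or that 280 is too small. The documents do not support either: positive correlation raises the power, and a correlation of 0.1 to 0.2 roughly absorbs a 10% to 20% loss. Loss during the 30-day telephone follow-up does not touch a comparison that ends at discharge.

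Two other readings also fail. A relative 10% (28% to 25.2%) would need about 3,909 per group by the two-sample formula, so 280 itself shows that an absolute difference was meant. Nor is 280 two comparison groups of 140: the 140 is per site, and the design is a single pre-post group.

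It can also be said that a PIM percentage and an incidence do appear in the article, and that a condensed article may leave the formula, discordance and dropout allowance to the full protocol. The second part is fair, and those omissions are not held against the plan. The first part goes only some way: neither term is defined as the proportion of patients with a PIM, and neither is in the end point list. Finally, the article does not tie the chi-square or Fisher test expressly to the admission-discharge comparison. They are, however, the only tests it names for frequencies.

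**Conclusion.** The point holds as a mismatch between the sample size, the end points and the test. The 280 is correct for a two-sided paired comparison of 28% with 18%, and it is adequate. What needs correcting is that the binary proportion behind it is not a listed end point, and that the named frequency tests ignore the pairing.

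Using chi-square or Fisher does not inflate the false-positive rate when the correlation is positive. It makes the test too strict and costs about 7 points of power at a correlation of 0.3 (91.6% − 84.7%) and 9 points at 0.5 (97.5% − 88.6%). At zero correlation there is practically no difference. These figures rest on an absolute 10-point effect, a two-sided 5% level, 280 evaluable pairs and an assumed range of correlations, since the article gives none. Because the end point concerned is secondary and the sample size need not change, this is a worthwhile correction rather than a threat to the study.

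**What to change.** Keep 280, and make these changes:

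1. In the sample size section, state that the 10% is an absolute difference (28% to 18%) in the proportion of patients with at least one PIM, tested two-sided at 5%.
2. Add that proportion, admission against discharge, to the secondary end points beside the count and the MAI score.
3. Analyse it with McNemar's test (two-sided 5%) in place of chi-square or Fisher.
4. Say that the 80% applies to this end point, at zero within-patient correlation and with 280 evaluable pairs.

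The cost is a few reworded sentences and one derived variable. STOPP/START is already applied at admission and discharge for every patient (Table 1), so no further patients, visits or data are needed. If recruitment is under way, the change should be dated and made before the outcome data are examined.

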### Description of CMR Interventions During the Phase 3 Study

#### Screening Phase

Prescriptions of both male and female older patients (aged 60 years and older) admitted to any medical or surgical ward at both study sites will be assessed to determine whether participants meet the eligibility criteria after the medical records are reviewed.

#### Study Enrollment Phase

Once potential participants are deemed eligible, we will proceed with the enrollment process. The collection of baseline data on participants’ medication profiles, medical history, and other relevant information will be performed. The participants’ demographic details and contact information for follow-up will also be documented. Using tools such as MAI and START/STOPP criteria, we will evaluate the incidence of inappropriate medications after 24 hours of admission at baseline and during hospitalization every third day.

#### Intervention Phase

CMR interventions as per the standard operating procedure will be applied, and all the relevant details mentioned in the CMR activities checklist will be executed. The clinical pharmacists will perform the activities and discuss them with the CMR team, and their suggestions will be presented to the treating physician in written format.

#### Follow-Up Phase

At discharge, the clinical pharmacist will assess the discharge prescription for the MAI score and potentially inappropriate medications. The percentage of acceptance of the suggestions given (by the CMR team during the admission) by the clinicians will also be recorded from the patient records. After discharge, the patients will be telephonically followed up by a trained field investigator for 30 days to inquire about any hospital admissions, visits to the emergency department, drug-related complications, and episodes of dizziness and falls. The AT-HARM10 tool will be used to identify the medication-related hospital admissions after discharge after obtaining the necessary permission from the authors. The detailed description of the study evaluations/measurements/assessments at various time points after CMR intervention is shown in Table 1.

A comparison of MAI scores and the incidence of potentially inappropriate medications before and after CMR intervention at admission and at discharge will predict the efficacy of CMR.

**Table 1 table1:** Description of the study evaluations/measurements/assessments after collaborative medication review intervention.

Event time points			Hospital admission (day 1)		During hospitalization (every third day until discharge)		Hospital discharge		
							Day X^a^		Day 30^b^
**Enrollment**									
	Eligibility screening	✓							
	Informed consent	✓							
**Screening prescriptions**									
	START^c^/STOPP^d^ criteria	✓		✓		✓			
	MAI^e^ score	✓		✓		✓			
**Intervention (CMR^f^)**									
	Medication history	✓		✓		✓			
	Medication reconciliation	✓		✓		✓			
	Medication review	✓		✓		✓			
	Collaborative team meeting	✓		✓		✓			
**Assessments**									
	CMR team time	✓		✓		✓			
	Cost analysis	✓		✓		✓			
	Drug-related problem	✓		✓		✓		✓	
	Hospital admissions							✓	

^a^X refers to the day of discharge of the patient from hospital since admission.

^b^Day 30 refers to 30th day after discharge.

^c^START: Screening Tool to Alert to Right Treatment.

^d^STOPP: Screening Tool for Older Persons’ Prescriptions.

^e^MAI: Medication Appropriateness Index.

^f^CMR: collaborative medication review.

### Process Indicators of Intervention

The following methods have been used to assess the feasibility of implementing interdepartmental CMR: (1) number of interdepartmental CMR meetings, (2) number of CMR consultations per patient, (3) percentage of medication discrepancies/medication-related adverse events identified, prevented, or resolved, and (4) percentage of suggestions given by the CMR team.

### Study End Points

#### Primary End Point

The primary end point was the facilitators and barriers in implementing interdepartmental CMR to reduce potentially inappropriate medications.

#### Secondary End Points

The secondary end points were as follows:

Costs involved in the implementation of CMR in Indian health care settings (tertiary health care settings perspective).Change in the number of potentially inappropriate medications from hospital admission to discharge due to CMR.Change in the MAI score from hospital admission to discharge due to CMR.Number of medication-related hospital admissions from the day of discharge to 30 days post discharge.

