##### Quantitative Component

The study design was quasi-experimental preinterventional and postinterventional with the following components: (1) costs incurred for the implementation of CMR in Indian health care settings and (2) MAI, reduction in the percentage of inappropriate medications, postdischarge adverse events, and medication-related admissions.

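### The efficacy outcome for potentially inappropriate medications is a count in one section, a percentage, an incidence or a prevalence in others, and the sample size fits a proportion rather than the listed count

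*Protocol article*

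**What the plan says.** All places are in the protocol article. PIM stands for potentially inappropriate medication.

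- **Secondary End Points:** "Change in the number of potentially inappropriate medications from hospital admission to discharge due to CMR", a number with no denominator. The next item is "Change in the MAI score from hospital admission to discharge due to CMR".
- **Study Design, Quantitative Component:** the outcomes are "MAI, reduction in the percentage of inappropriate medications, postdischarge adverse events, and medication-related admissions". PIM is a percentage here, and the article does not say of what.
- **Study Enrollment Phase and Follow-Up Phase:** PIM is an incidence. The Follow-Up Phase bases efficacy on "A comparison of MAI scores and the incidence of potentially inappropriate medications before and after CMR intervention at admission and at discharge".
- **Sample Size Estimation and Analysis:** the calculation starts from an earlier study in which "the prevalence of potentially inappropriate medications in the older adult population was 28% in India", with an effect size of 10%, power of 80% and a 5% significance level, giving 280 participants.
- **Data Management and Statistical Analyses, Quantitative Component:** a paired one-sided t test "will be used to analyze the differences between MAI scores at admission and discharge to determine the effectiveness of CMR". For everything else, "the chi-square test or Fisher exact test will be used to assess the differences in the frequency distribution". No test is named for a change in a PIM count.

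**The concern.** A count per patient, the share of a patient's drugs that are inappropriate, and the share of patients with at least one inappropriate drug are three different quantities. They need different tests and different sample-size inputs, and they can move in different directions in the same patient.

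The choice matters in this design. Baseline is scored after 24 hours of admission, on an inpatient drug list from any medical or surgical ward. The comparison is the discharge prescription. The number of drugs can change between the two for reasons unrelated to the review, and the design is pre-post with no comparator described.

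If the measure is not fixed in advance, the analyst can choose among the versions after seeing the data, and each choice could be defended by citing a section of the article. PIM is one of the efficacy outcomes that the 280 patients are recruited to assess.

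**Working it through.** **Step 1: reproduce 280.** Inputs from the article: 28%, effect size 10%, power 80%, significance level 5%. Assumptions, because the article gives no formula: the 10% is an absolute fall to 18%, the test is two-sided, and the two time points are paired with zero correlation.

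- Both time points positive: 0.28 × 0.18 = 0.0504
- Discordant cells: 0.28 − 0.0504 = 0.2296 and 0.18 − 0.0504 = 0.1296, total 0.3592
- n = (1.960 × √0.3592 + 0.842 × √(0.3592 − 0.10²))² / 0.10² = (1.1747 + 0.4973)² / 0.01 = 279.6, rounded up to **280 pairs**

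Alternatives:

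- Two independent proportions, 28% against 18%, two-sided: 277 per group, close to 280 only if 280 is a per-group figure.
- The same McNemar calculation one-sided: 220 pairs.
- A relative 10% fall (28% to 25.2%), two independent proportions, two-sided: 3909 per group.
- The 10% read as a standardised paired change of 0.10: (2.80 / 0.10)², that is 785 pairs two-sided, or 619 one-sided.

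The match is not unique, since other combinations of formula and drop-out allowance also come near 280. But the stated inputs lead directly to it as a change in a paired proportion, and the article gives no mean or SD of a PIM count from which a count-based size could be derived.

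**Step 2: what the 28% describes.** The Introduction and the sample-size section both give it as a prevalence in the older population. That reads as a share of people, not a share of drugs or a count per person.

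**Step 3: do the measures agree?** The article gives no drug counts, so the following patients are assumed for illustration.

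| Admission → discharge | Count | Share of drugs | At least one PIM |
|---|---|---|---|
| 2 of 8 → 2 of 6 (two appropriate drugs stopped) | unchanged | 25% → 33% | yes → yes |
| 4 of 10 → 2 of 5 | halved | 40% → 40% | yes → yes |
| 2 of 8 → 2 of 9 (one appropriate drug added) | unchanged | 25% → 22% | yes → yes |
| 1 of 5 → 0 of 4 (the PIM stopped) | 1 → 0 | 20% → 0% | yes → no |

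The three measures agree on improvement only in the last row. In the first, the share worsens while the other two do not move. In the second, only the count improves. In the third, only the share improves.

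**Step 4: match to the tests.** The paired t test is named for MAI only. Chi-square and Fisher tests compare frequencies, so they do not test a mean change in a count. Applied to admission against discharge, they would also ignore that the same patients appear twice.

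**Step 5: what 280 supports under each choice.** For patients with at least one PIM, 280 pairs suffice at zero correlation. With positive within-patient correlation fewer are needed: 199 at 0.3 and 145 at 0.5. For a mean change in count, 280 pairs give 80% power, two-sided, for a change of 2.80 / √280 = 0.167 SD of the paired differences. What that is in drugs cannot be derived from the article.

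**The case against.** The outcomes are secondary, and the primary end point is facilitators and barriers. The percentage appears in a one-line design list, so a reader could take the formal end-point list as authoritative. A count also fits the stated aim of reducing such medications. A full protocol or SAP, not shown, may define everything. These points limit the weight of the finding, but an SAP that picks one measure does not make the article's sections agree, and if the count is authoritative, the sample size and the listed tests do not match it.

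Several stronger readings are tempting, and the documents do not support them.

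- **That the MAI change is not standardised for the number of drugs.** The article says only MAI score and does not describe how it is aggregated. An article commonly leaves that detail out. A dependence on drug number would arise only if item scores are summed over a patient's drugs.
- **That the PIM count falls whenever drugs are stopped at discharge.** It falls only if a stopped drug was itself a PIM, and stopping such a drug may be exactly what the review intended. The first row of the table shows a count that does not move.
- **That 28% of drugs are inappropriate, so a shorter list lowers the count in proportion.** The 28% reads as a share of people.
- **That efficacy should be claimed only if the per-drug figure improves.** The second row shows PIMs halved with an unchanged share, so such a rule could reject real benefit. Dividing by the number of drugs also does not replace a comparator.

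**Conclusion.** The inconsistency stands. The PIM outcome is a number, a percentage without denominator, an incidence and a prevalence in different sections. The sample size fits a change in a paired proportion from 28% to 18%, and the listed tests do not address a change in a count. The 280 match rests on an absolute 10-point fall, a two-sided test and zero correlation, none of which the article states.

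The size of any effect on the result cannot be computed, because no drug counts or PIM distributions are given. The assumed patients show only that the measures can disagree, including in direction. The point is worth correcting before analysis because it removes a post hoc choice of efficacy measure, but it concerns secondary end points and does not show that any one measure is biased.

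**What to change.** 1. Name one PIM measure with its denominator as the end point. Use it in Secondary End Points, the design list, Study Enrollment Phase, Follow-Up Phase, the sample-size section and the statistical analysis section.
2. Name a paired test that matches. For example, use McNemar for the proportion of patients with at least one PIM, which is what 280 supports. If the count is kept, name a paired analysis of the count and restate the sample size with an assumed mean change and SD.
3. State in the sample-size section that the 10% is absolute (if so), whether the test is one-sided or two-sided, and the formula used.
4. State how the MAI score is aggregated over a patient's drugs.
5. Report the number of drugs at admission and discharge. As supporting results, give PIMs as a per-patient total and per drug, and do the same for MAI if it is summed per patient.

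The cost is end-point wording and one division, because the drug list is already being scored at both times. The small downside is that a per-drug figure can hide benefit from stopping drugs, so it should be descriptive and not a condition for claiming efficacy.

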## Discussion

This study will assess the feasibility of implementing CMR in Indian hospitals and identify the key facilitators and barriers to CMR implementation. This study will evaluate the potential for reducing potentially inappropriate medications and medication-related admissions while providing crucial cost-implementation data for the Indian health care context.

Although CMR implementations have been well-studied in Western health care settings, with documented reductions in potentially inappropriate medications and readmissions, this will be among the first studies to systematically evaluate CMR feasibility and implementation costs in Indian health care settings [3,8,13-17]. The protocol’s mixed methods approach will help bridge the knowledge gap between established Western practices and the unique challenges of the Indian health care system. By adopting a health system perspective for economic evaluation, this study will generate data of direct relevance to policy makers and administrators. However, purposive sampling in the qualitative component may introduce selection bias, and the exclusive focus on tertiary care settings may limit the generalizability of the findings to primary or rural health care facilities. Additionally, the relatively short follow‑up period proposed in this protocol will constrain our ability to assess the long‑term sustainability and downstream clinical effects of CMR.

Upon completion of this study, subsequent research will aim to develop and pilot standardized training modules for clinical pharmacists, ensuring consistency in CMR workflows across institutions. Finally, the findings will inform the creation of national guidelines and policies to support the systematic integration of CMR into regular clinical practice throughout India. Policy briefs summarizing key recommendations will be developed for the Ministry of Health and Family Welfare and relevant state health departments.

The findings of this study will redefine medication management practices and pave the way for evidence-based, scalable models of CMR in resource-constrained settings. It will underscore the need for cross-disciplinary collaboration as a fundamental strategy to address multimorbidity in older adult populations, thereby offering valuable insights for policy makers and health care providers aiming to optimize geriatric care.

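### The admission-to-discharge changes in MAI and inappropriate medications are defined as effects of CMR, but the single-group design has no comparator that could separate CMR from ordinary in-hospital change

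*Protocol article*

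**What the plan says.** Under Study Design, the article states: "The study design was quasi-experimental preinterventional and postinterventional with the following components". The components are costs and "MAI, reduction in the percentage of inappropriate medications, postdischarge adverse events, and medication-related admissions". The sample of 280 is split as 140 per site, not by arm (Sample Size Estimation and Analysis). No control ward, control group or pre-implementation period is described. Table 1 ticks every CMR component at admission (day 1), every third day, and at discharge.

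The attribution to CMR is made in three places:

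- Secondary End Points: "Change in the MAI score from hospital admission to discharge due to CMR" and "Change in the number of potentially inappropriate medications from hospital admission to discharge due to CMR".
- Follow-Up Phase: the comparison of MAI scores and PIMs at admission and at discharge is said to predict the efficacy of CMR.
- Data Management and Statistical Analyses, Quantitative Component: a one-sided paired t test is applied to "differences between MAI scores at admission and discharge to determine the effectiveness of CMR".

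On who scores, the Intervention Phase says: "The clinical pharmacists will perform the activities and discuss them with the CMR team". The Follow-Up Phase says: "At discharge, the clinical pharmacist will assess the discharge prescription for the MAI score and potentially inappropriate medications". The Introduction classes MAI as an implicit, judgment-based tool.

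Medication-related admissions are counted from discharge to day 30 only (Secondary End Points; Table 1). The Abstract's Objective lists them among the measures of efficacy, and the Discussion says: "This study will evaluate the potential for reducing potentially inappropriate medications and medication-related admissions".

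**The concern.** The baseline score is taken after 24 hours of admission, on an acute inpatient chart. The final score is taken on the discharge prescription. These are different kinds of document. Acute drugs may be stopped and home drugs restarted or reconciled under usual care, and patients with a poor first score may regress toward the mean. The planned contrast measures all of this plus any effect of CMR, yet the end point definition assigns the whole of it to CMR.

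The Discussion intends the findings to feed national guidelines and policy briefs. Its limitations name purposive sampling, the tertiary setting and short follow-up, but neither the missing comparator nor the source of the scores. A significant paired test would therefore be read as evidence that CMR works, when it shows only that prescriptions changed during the stay.

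**Working it through.** **1. The plan's own figure.** Inputs from Sample Size Estimation and Analysis: 28% prevalence, effect 10%, power 80%, significance 5%. If the effect is read as an absolute fall to 18% and the test as two-sided, the two-proportion formula gives

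n = [1.96·√(2·0.23·0.77) + 0.8416·√(0.28·0.72 + 0.18·0.82)]² / 0.10² = (1.1665 + 0.4973)² / 0.01 ≈ 277 per group or time point.

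A paired calculation with independent admission and discharge status has discordant probability 0.28·0.82 + 0.18·0.72 = 0.3592, so

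n = [1.96·√0.3592 + 0.8416·√(0.3592 − 0.01)]² / 0.01 ≈ 280.

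So 280 fits one group measured twice. The arithmetic is not the problem, but the sample is sized to detect a before-after change, whatever its cause.

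**2. What the planned MAI test does when CMR has no effect.** Let dz be the usual-care MAI change in the favourable direction, divided by the SD of the paired difference. The protocol gives no MAI mean or SD, so dz is an assumption and a range is shown. With n = 280, √280 = 16.733, and a one-sided 5% test,

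P(significant) ≈ Φ(dz·16.733 − 1.645).

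| dz (assumed) | dz·√280 | P(significant), zero CMR effect |
|---|---|---|
| 0 | 0 | 0.05 |
| 0.05 | 0.837 | 0.21 |
| 0.10 | 1.673 | 0.51 |
| 0.15 | 2.510 | 0.81 |
| 0.20 | 3.347 | 0.96 |

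The noncentral t distribution gives the same values to two decimals, apart from 0.80 at dz = 0.15 and 0.95 at dz = 0.20. A drift of one tenth of an SD is enough for an even chance of a significant result.

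**3. Can another planned measurement supply the contrast?** The third-day assessments cannot, because Table 1 starts CMR on day 1 and there is no CMR-free stretch. The site split cannot, because both sites deliver CMR. The recorded acceptance of suggestions could help describe which changes followed CMR advice, but it is not used in the efficacy analysis.

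**4. Who scores.** Set side by side, the Intervention Phase and the Follow-Up Phase give delivery of CMR and discharge scoring to the same role. No masking or separation is stated, and the main score is judgment-based.

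**5. Medication-related admissions.** There is one observation window, discharge to day 30, no earlier window and no comparison group. What can be estimated is a proportion. For example, a hypothetical 14 of 280 would be 5.0%, exact 95% CI 2.76% to 8.25%. A reduction has no reference value.

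**The case against.** The strongest reply is that efficacy is secondary. The primary objective is feasibility, the primary end point is facilitators and barriers, and the article openly calls the design quasi-experimental and before-after. An article also condenses, and the standard operating procedures that may say who scores what are not shown. This bears on the weight of the point. It does not remove it: the attribution sits in the end point definition itself, and no later analysis of admission and discharge scores alone can supply the missing contrast.

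Four stronger readings are tempting, and the document does not support them.

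- A reader might infer that the same individual gives the advice and scores the result. The text shows only the same role; it neither states nor excludes the same person.
- A reader might put a false-efficacy rate on the PIM outcome with a paired McNemar test: for a usual-care fall from 28% to 18%, 0.80 at zero within-patient correlation and 0.97 at 0.5. The article names chi-square or Fisher tests, not McNemar, and the end point is the number of PIMs, not their prevalence. The unpaired chi-square test in the same scenario rejects in about 81% to 89% of trials. For a fall to 23%, it rejects in about 27%, dropping to 20% as the correlation rises. No usual-care fall is given in the document, so the verdict does not rest on these figures.
- A reader might take items resolved after an accepted suggestion as an upper bound for the CMR effect. Reconciliation and team meetings belong to CMR in Table 1, and problems prevented are among the process indicators. These can act without a recorded suggestion, so the bound fails.
- A reader might fault the admissions end point itself. As defined it is a plain count with no attribution and no stated test. Only the efficacy and reduction language around it goes too far.

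**Conclusion.** The point holds as a fault of attribution. One group, treated from day 1 and compared with itself, cannot show that a change in MAI or PIMs is caused by CMR, yet the end points, the Follow-Up Phase and the analysis section all say that it does. With no CMR effect, the chance of a significant MAI test runs from 0.05 with no usual-care change to about 0.96 at a usual-care change of 0.20 SD. These values rest on assumed drift, an approximately normal mean difference and all 280 patients analysed. They do not show that drift of that size will occur, nor that CMR is ineffective. The shared role of deliverer and scorer adds a risk of bias whose size cannot be derived from the document. The admissions outcome is sound as a description and unsupported as evidence of a reduction. Because efficacy is secondary, this should be corrected but does not undermine the study's primary purpose.

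**What to change.** 1. In Secondary End Points, the Follow-Up Phase and the Quantitative Component of the analysis section, replace the wording on *due to CMR*, *efficacy* and *effectiveness* with change from admission to discharge during a stay with CMR, reported as an estimate with a 95% CI. In the Discussion, name the missing comparator and the non-independent scoring as limitations. Cost: wording only.
2. Report medication-related admissions as a proportion with an exact 95% CI. Remove the efficacy wording for them in the Objective and the reduction wording in the Discussion. In Results, replace the planned cost-effectiveness calculations, which also lack a comparator, with implementation cost per patient. Cost: wording and a simple analysis.
3. Where suggestions can be linked to individual items, report separately the PIM or MAI items resolved after an accepted suggestion, labelled CMR-linked change, as a description only. The article mentions a percentage of acceptance and no item-level link, so this needs a little extra data linkage.

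A concurrent comparator is not proposed within the present sample: 28% against 18% needs 277 per arm (554 in total), and 140 per arm would have about 51% power (two-sided 5%). The downside of the changes above is a more modest efficacy claim.
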